## Abstract

Background: Airway assessment plays an important part in airway management. Over the years, ultrasound has emerged as an alternative modality for airway assessment. We aim to assess the accuracy of clinical parameters, ultrasonographic upper airway parameters, and laryngoscopic grade, using the Cormack-Lehane classification, to predict difficult laryngoscopy in the emergency department (ED). The primary objective is to determine the accuracy of ultrasonography parameters compared to Cormack-Lehane grading in predicting difficult laryngoscopy in adults. The secondary objective is to assess the accuracy of clinical parameters compared to Cormack-Lehane grading in predicting difficult laryngoscopy in adults.

Methods: A sample of 62 adult patients over 18 years who come to the emergency department and require endotracheal intubation will undergo an ultrasonographic examination of the upper airway. During this examination, an emergency medicine physician will measure the skin-to-epiglottis distance and tongue thickness using the GE Healthcare (Chicago, IL) ultrasound and color Doppler (model: Logic E).

Results: The results of the study will be drawn in 2025 upon its completion.

Conclusions: The conclusion will be drawn regarding the correlation between ultrasound parameters and Cormack-Lehane grading and clinical parameters in predicting difficult laryngoscopy.

## Introduction

Effective airway management is crucial for patients in critical conditions. However, it remains a challenge in the emergency department (ED). Loss of control of the airway can lead to catastrophic effects. Airway assessment plays an important part in airway management [1]. Predicting difficult airways is often hampered in the ED. Traditionally used clinical parameters such as Look externally, Evaluate the 3-3-2 rule, Mallampati score, Obstructed airway, and Neck mobility (LEMON) have limitations in emergency settings due to factors like uncooperative patients, cervical spine immobilization, and obtunded patients [2]. Ultrasound has emerged as an alternative modality for airway assessment in recent years, as it is a mobile, noninvasive, and nonionizing technology [3].

Ultrasound allows real-time visualization of anatomical structures, aiding in rapid assessment. It helps gauge parameters like airway patency, identify potential obstructions, and assess the position of vocal cords. This dynamic imaging enhances decision-making during interventions such as intubation through optimal preparation involving appropriate choice of equipment and personnel, making the process more precise and reducing complications [4].

The Cormack-Lehane classification is the gold standard for defining difficult laryngoscopy. Hence, airway assessment parameters have classically been compared to the Cormack-Lehane classification [5]. The literature search revealed multiple studies comparing clinical assessment indices versus ultrasound parameters in preoperative settings. However, studies in emergency settings are limited [6]. This research delves into the comprehensive use of ultrasound in airway management in emergency settings through clinical parameters like LEMON criteria, ultrasound measurements like skin-to-epiglottis distance, tongue thickness, and Cormack-Lehane classification on direct laryngoscopy as key metrics.

## Materials and methods

Study design and setting

This will be a prospective cross-sectional study of adult patients coming to the ED requiring endotracheal intubation. After obtaining ethical and research clearance from the Ethics Committee at the Datta Meghe Institute of Higher Education and Research, the study will be conducted in Acharya Vinoba Bhave Rural Hospital. Informed consent will be obtained from study participants. A trained Emergency Medicine physician unaware of the clinical and ultrasound airway parameters will perform a laryngoscopy and record Cormack-Lehane grading.

Inclusion criteria

Patients 18 years old and older who need endotracheal intubation will be included.

Exclusion criteria

Patients with limited mouth opening, head and neck pathologies, and upper airway anatomical anomalies, trauma, or tumors will be excluded. Patients who have undergone tracheostomy, pregnant patients, and those with limited neck extension will be excluded from the study.

Statistical analysis

A sample size of 62 is derived based on the article by Sotoodehnia et al. [1]. The estimated proportion with absolute precision is as follows: alpha (α) = 0.05, estimated proportion (p) = 0.799, and estimation error (d) = 0.10.

Procedure

Clinical airway assessment of patients in a supine position will be done using LEMON criteria, and findings will be noted. All enrolled patients will undergo a duly explained ultrasonographic examination of the upper airway. Ultrasound-guided parameters will be measured using GE Healthcare (Chicago, IL) ultrasound and color Doppler (model: Logic E) curvilinear transducer. The parameters like skin-to-epiglottis distance and tongue thickness will be measured. To begin with, the probe will be placed in the midline, and then the neck scanning will be done in the transverse plane, scanning plane sections through both the vocal cords, from the cephalad to the caudal direction. The thickness of the anterior soft tissue will be measured at the level of the vocal cord, from the skin to the epiglottis. Tongue thickness will be defined as the maximum vertical length measured from the tongue surface to the submental skin.

Ethical approval

Approval is sought from the Ethical Committee of the Datta Meghe Institute of Higher Education and Research under approval no. DMIHER(DU)/IEC/2024/193 and the Clinical Trials Registry of India (CTRI) under CTRI no. CTRI/2024/06/069097. Written informed consent will be obtained from all patients included in the study.

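### The sample size of 62 gives ±0.10 only for a proportion taken over all 62 patients; the protocol does not say that 0.799 is such a measure, and sensitivity, specificity or AUC would be less precise

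*Protocol article*

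**What the plan says.** The protocol article gives its sample-size basis under Materials and methods, Statistical analysis. It reads "A sample size of 62 is derived based on the article by" a cited study, and then "The estimated proportion with absolute precision is as follows": "alpha (α) = 0.05", "estimated proportion (p) = 0.799, and estimation error (d) = 0.10". Nothing further is said about what the 0.799 measures, and no expected share of difficult laryngoscopies appears there or elsewhere.

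The Abstract sets the target: "The primary objective is to determine the accuracy of ultrasonography parameters compared to Cormack-Lehane grading in predicting difficult laryngoscopy in adults". The Introduction names the reference standard: "The Cormack-Lehane classification is the gold standard for defining difficult laryngoscopy". The 62 are not selected by difficulty; under Inclusion criteria, "Patients 18 years old and older who need endotracheal intubation will be included".

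**The concern.** A precision calculation serves an objective only if its denominator is the denominator of the quantity to be estimated. For a diagnostic-accuracy objective the usual quantities split the sample. Sensitivity uses only the patients whose laryngoscopy proves difficult, and specificity only those whose laryngoscopy proves easy. The AUC uses all patients, but its variance depends on the size of both groups and is not binomial. A calculation with one proportion and no prevalence serves none of these three at the stated precision.

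The paragraph is the protocol's only quantitative justification of its size. A reader would take ±0.10 as the precision of the primary result, while the number of difficult cases behind a sensitivity might be a small fraction of 62. The exclusion criteria may reduce it further, since "Patients with limited mouth opening, head and neck pathologies, and upper airway anatomical anomalies, trauma, or tumors will be excluded". A missed difficult airway is the costly error in this setting, so the precision of sensitivity is what a reader would most want to know.

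**Working it through.** **Inputs from the protocol article.** N = 62, alpha = 0.05, p = 0.799, d = 0.10 (Materials and methods, Statistical analysis). Sidedness is not stated.

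**Step 1: reproduce the plan's figure.** Single-proportion precision formula, n = z² p(1 − p) / d²:

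- Two-sided, z = 1.96: 1.96² × 0.799 × 0.201 / 0.10² = 61.7, rounded up to 62. This matches.
- A one-sided 5% level gives 43.5, so 44, which does not match.
- Half-width at n = 62: 1.96 × √(0.799 × 0.201 / 62) = 0.0998.

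So 62 is reached with all patients in the denominator, no prevalence term and no allowance for losses.

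**Step 2: assumption.** The documents give no prevalence of difficult laryngoscopy. I take 10%, 20%, 30% and 50%, which in whole patients are 6, 12, 19 and 31 difficult cases and 56, 50, 43 and 31 easy ones. In each calculation below the true value of the measure is taken as 0.799.

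**Step 3: half-widths at N = 62.**

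- Sensitivity: 1.96 × √(0.799 × 0.201 / number difficult). For example, with 12 difficult: 1.96 × √(0.1606 / 12) = 0.227.
- Specificity: the same with the number easy. For example, with 50 easy: 1.96 × √(0.1606 / 50) = 0.111.
- AUC: 1.96 × the Hanley-McNeil standard error, with Q1 = A/(2 − A) = 0.665 and Q2 = 2A²/(1 + A) = 0.710 at A = 0.799. The standard errors are 0.112, 0.081, 0.067 and 0.057.

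| Assumed prevalence | Difficult / easy | Sensitivity | Specificity | AUC |
|---|---|---|---|---|
| 10% | 6 / 56 | ±0.32 | ±0.105 | ±0.22 |
| 20% | 12 / 50 | ±0.23 | ±0.11 | ±0.16 |
| 30% | 19 / 43 | ±0.18 | ±0.12 | ±0.13 |
| 50% | 31 / 31 | ±0.14 | ±0.14 | ±0.11 |

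**Step 4: exact (Clopper-Pearson) intervals for sensitivity**, because the normal approximation is poor with so few cases: 5/6 gives 0.36 to 1.00; 10/12 gives 0.52 to 0.98; 15/19 gives 0.54 to 0.94; 25/31 gives 0.63 to 0.93 (upper limit 0.925).

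**Step 5: the multiplier.** For sensitivity the half-width grows by 1/√prevalence: about 3.2 at 10%, 2.2 at 20%, 1.8 at 30% and 1.4 at 50%. It equals 2 at a prevalence of 1/4 and 3 at 1/9 (11%).

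**The case against.** The strongest reply is that the protocol contains no error of calculation and never claims ±0.10 for sensitivity. It attaches 0.10 to an unnamed proportion and calls the objective accuracy. If 0.799 is the overall proportion correctly classified, the denominator is all 62 and ±0.10 is correct. If it is a specificity, the shortfall is small at low prevalence: ±0.105 to ±0.12 between 10% and 30%. The label on 0.799 may also stand in the cited study or in a fuller protocol, neither of which is shown.

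Much of this stands. 62 follows from its inputs, and the overall-accuracy reading is open. That reading would still serve the objective weakly: at an assumed 20% prevalence, calling every patient easy is already right 80% of the time.

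Two stronger readings are tempting and should not be drawn:

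- A reader might infer that sensitivity will be estimated two to three times less precisely than the plan states. The plan states nothing about sensitivity, and that factor needs a prevalence of about 11% to 25%, which the documents do not give.
- A reader might infer that a sensitivity near 0.80 could not be told apart from 0.50. Of the four scenarios, only the one at 10% has an exact interval that includes 0.50; the intervals at 20%, 30% and 50% exclude it.

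The reply does not remove the core. The article does give its sample-size basis with all its inputs, and that basis is not tied to the stated objective. This is not detail left to an analysis plan.

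**Conclusion.** The point holds in conditional form. ±0.10 at N = 62 is right for a proportion over all 62 patients. It is not met for sensitivity or specificity of 0.799 whenever the sample contains both difficult and easy cases, and it is not met for an AUC of 0.799 at any prevalence examined. The size of the gap depends on which measure is meant and on the prevalence. Sensitivity is affected most (±0.14 to ±0.32 over assumed prevalences of 50% down to 10%), the AUC less (±0.11 to ±0.22), and specificity least at low prevalence (±0.105 at 10%). All these figures assume a true value of 0.799 and a prevalence range that is mine, not the protocol's. The number 62 itself is not wrong; what is wrong as written is the implied precision for the primary objective.

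**What to change.** Keep N = 62 and rewrite the sample-size paragraph:

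- Say which measure 0.799 is.
- State the assumed prevalence of difficult laryngoscopy and its basis.
- Replace the implied ±0.10 for the primary objective with the expected 95% half-widths at N = 62 for sensitivity and specificity, and for the AUC if it is used. At an assumed 20% these would be about ±0.23, ±0.11 and ±0.16.
- Keep ±0.10 only if it is explicitly tied to the overall proportion correctly classified.

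The change needs no extra patients and alters no procedure. Its cost is that the stated precision becomes less favourable. Switching to the AUC as primary measure would not restore ±0.10, and the choice of primary measure and interval method can be left to the analysis plan.

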## Discussion

Traditionally, various clinical parameters such as thyromental distance, Mallampati score, and neck circumference have been employed to anticipate challenging airways. However, these methods while useful have limitations in emergent situations where rapid and accurate assessment is paramount [7-10]. This study evaluates the comparative effectiveness of airway ultrasound versus conventional clinical parameters in predicting difficult laryngoscopy within an ED setting [3,11,12]. Airway ultrasound has demonstrated significant potential over time due to its noninvasiveness, real-time imaging capabilities, and its ability to visualize anatomical structures that may not be readily accessible through clinical examination alone. Several studies have highlighted the potential of ultrasound parameters such as the distance from the skin to the epiglottis, the anterior neck soft tissue thickness at the level of the hyoid bone and vocal cords, and the visibility of the hyoid bone in predicting difficult laryngoscopy. These parameters can provide detailed insights into airway anatomy, offering an additional layer of assessment that may enhance the accuracy of predicting a difficult airway [13].

This research will evaluate both airway ultrasound and traditional clinical examination parameters in a cohort of patients presenting to the ED in a prospective cross-sectional study design. Participants will undergo a comprehensive assessment that includes both methods before laryngoscopy. The outcomes of these assessments will then be compared to the actual laryngoscopy grade, which serves as the gold standard for determining airway difficulty [14,15].

One of the primary advantages of using a prospective cross-sectional study design is its ability to provide real-time, context-specific data. In the dynamic and often unpredictable environment of the ED, having reliable and immediately applicable predictive tools is essential. By directly comparing ultrasound findings with clinical examination results and correlating them with laryngoscopic outcomes, this study aims to determine the most accurate and practical method for anticipating difficult airways [3].

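### The only sentence that can define skin-to-epiglottis distance joins a vocal-cord level to an epiglottis end point, which the article elsewhere lists as two separate parameters

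*Protocol article*

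**What the plan says.** The Abstract sets the aim: "The primary objective is to determine the accuracy of ultrasonography parameters compared to Cormack-Lehane grading in predicting difficult laryngoscopy in adults". It then names the ultrasound measurements: "an emergency medicine physician will measure the skin-to-epiglottis distance and tongue thickness". The Introduction lists the same two among its key metrics, and the Procedure under Materials and methods repeats them: "The parameters like skin-to-epiglottis distance and tongue thickness will be measured".

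The Procedure next describes the scan. The probe starts in the midline and the neck is scanned transversely, with "scanning plane sections through both the vocal cords, from the cephalad to the caudal direction". The measuring rule follows: "The thickness of the anterior soft tissue will be measured at the level of the vocal cord, from the skin to the epiglottis". Tongue thickness then has its own sentence with its own two end points.

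The Discussion, listing ultrasound predictors highlighted in earlier studies, gives as separate items "the distance from the skin to the epiglottis, the anterior neck soft tissue thickness at the level of the hyoid bone and vocal cords".

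**The concern.** A distance on an image needs a level and two end points that go together. Here the level is the vocal cord and the deep end point is the epiglottis. By the article's own list in the Discussion, these belong to different parameters. The label used in the rule, a thickness of anterior soft tissue, also matches the cord-level parameter rather than the one named in the Abstract.

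This is an index measurement in an accuracy study. Any sensitivity, specificity or threshold reported for skin-to-epiglottis distance describes whatever distance was actually recorded. If that was a cord-level thickness, the result carries the wrong name. If it varied between patients, the result describes neither distance. Analysis cannot repair this later unless the level was noted for each scan.

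**Working it through.** The point is textual, so the check sets the statements side by side. The article's one design figure is reproduced first to see whether it is affected.

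**1. Sample size.** The inputs, from Statistical analysis, are "alpha (α) = 0.05, estimated proportion (p) = 0.799, and estimation error (d) = 0.10". The formula for estimating one proportion with absolute precision, taking alpha as two-sided, is n = z² × p × (1 − p) / d².

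- n = 1.96² × 0.799 × 0.201 / 0.10² = 61.69, rounded up to 62.
- This matches the stated 62. A one-sided alpha would give 43.45, which does not match.
- No ultrasound distance enters the formula, so 62 stands whichever distance is meant.

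**2. The statements compared.**

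| Place | Name used | Level | Deep end point |
|---|---|---|---|
| Abstract, Introduction, Procedure (list of parameters) | Skin-to-epiglottis distance | Not given | Epiglottis (by name) |
| Procedure (measuring rule) | Thickness of anterior soft tissue | Vocal cord | Epiglottis |
| Discussion, first item | Distance from skin to epiglottis | Not given | Epiglottis |
| Discussion, second item | Anterior neck soft tissue thickness | Hyoid bone and vocal cords | Not given |

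The measuring rule takes its name and level from the second Discussion item and its end point from the first.

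**3. Can another sentence define the parameter?** Two ultrasound measurements are named. Tongue thickness has its own definition. That leaves the measuring rule as the only sentence that can define skin-to-epiglottis distance.

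**4. Does any reading avoid the problem?**

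- *The rule defines skin-to-epiglottis distance.* Its level then conflicts with its end point.
- *The rule describes a third variable, a cord-level thickness.* Skin-to-epiglottis distance then has no definition, the third variable is missing from the Abstract, and its end point still does not fit its level.
- *The level phrase is a slip.* The intended parameter is then clear, but the sentence is wrong as printed.

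The sentence needs changing under all three.

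**5. What would be recorded?** An operator who follows the end point records skin-to-epiglottis distance and ignores the stated level. One who follows the level records a cord-level thickness under the other name. If practice varies between scans, the column holds both.

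**The case against.** The strongest reply is that the intention is plain. The Abstract, the Introduction and the Procedure all name skin-to-epiglottis distance, and the disputed sentence itself ends at the epiglottis. The sweep runs from head to foot, so it is not confined to one section at the cords. The Discussion list reports what other studies used and is not a second instruction. The Abstract's wording is also compatible with a single sonographer who reads the sentence the same way every time.

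Much of this stands. A misplaced level phrase is a plausible explanation, and the Discussion is background. It still shows that the article treats the two as different quantities. A single consistent reader does not remove the defect, because consistent measurement at the cords would still be reported under the wrong name. Nor is this detail left to a fuller protocol: the article states the rule, and states it inconsistently.

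Some stronger readings are tempting but not supported:

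- *That this is the main ultrasound measurement.* The primary objective speaks of parameters in the plural. Two are named and neither is ranked first. Tongue thickness is unaffected by this sentence.
- *That operators will disagree.* The number of sonographers is not given.
- *That a particular loss in area under the curve follows.* This would need the accuracy of each distance, the offset between them and the share of scans taken each way. The article gives none of these, and with unequal accuracies the answer also depends on which distance is the larger.
- *That thresholds will not be comparable with other studies.* The article states no threshold, and the other studies are not at hand.
- *That the scanning plane for tongue thickness must be added.* An article commonly leaves such detail to the full protocol.

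**Conclusion.** The concern holds as an internal inconsistency in the definition of one of the two ultrasound measurements named for the primary objective. As printed, the rule allows accuracy for a cord-level thickness to be reported as accuracy for skin-to-epiglottis distance, or the two to be mixed.

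The reach is one of two named index measurements, in up to all 62 planned patients. The sample size is unaffected, and no numerical loss of accuracy can be derived from the article. The conclusion rests on the article's wording alone, on reading the Discussion's list as naming distinct parameters, and on no fuller document having already corrected the sentence. It does not show that the wrong distance will be measured, only that the text permits it.

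**What to change.** Reconcile the measuring rule in the Procedure so that skin-to-epiglottis distance has one level, the section in which the epiglottis is seen, and one end point, the epiglottis. Use the same name there as in the Abstract. If soft tissue thickness at the vocal cords is also wanted, give it its own name, level and end point, and record and analyse it as a separate variable.

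The cost is one or two sentences and a matching field on the data sheet, with no added procedure and no change to the sample size. It is best settled before scans are recorded. For any scans already taken, note which level was used where that can be established.

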## Results

Data will be compiled in an Excel sheet (Microsoft Corporation, Redmond, WA) and analyzed using appropriate statistical tests. The results will be drawn in 2025 after the study is completed. A positive impact is expected, as ultrasound will become an essential tool in emergency airway management, enhancing patient safety and clinical outcomes.

## Discussion

Traditionally, various clinical parameters such as thyromental distance, Mallampati score, and neck circumference have been employed to anticipate challenging airways. However, these methods while useful have limitations in emergent situations where rapid and accurate assessment is paramount [7-10]. This study evaluates the comparative effectiveness of airway ultrasound versus conventional clinical parameters in predicting difficult laryngoscopy within an ED setting [3,11,12]. Airway ultrasound has demonstrated significant potential over time due to its noninvasiveness, real-time imaging capabilities, and its ability to visualize anatomical structures that may not be readily accessible through clinical examination alone. Several studies have highlighted the potential of ultrasound parameters such as the distance from the skin to the epiglottis, the anterior neck soft tissue thickness at the level of the hyoid bone and vocal cords, and the visibility of the hyoid bone in predicting difficult laryngoscopy. These parameters can provide detailed insights into airway anatomy, offering an additional layer of assessment that may enhance the accuracy of predicting a difficult airway [13].

This research will evaluate both airway ultrasound and traditional clinical examination parameters in a cohort of patients presenting to the ED in a prospective cross-sectional study design. Participants will undergo a comprehensive assessment that includes both methods before laryngoscopy. The outcomes of these assessments will then be compared to the actual laryngoscopy grade, which serves as the gold standard for determining airway difficulty [14,15].

One of the primary advantages of using a prospective cross-sectional study design is its ability to provide real-time, context-specific data. In the dynamic and often unpredictable environment of the ED, having reliable and immediately applicable predictive tools is essential. By directly comparing ultrasound findings with clinical examination results and correlating them with laryngoscopic outcomes, this study aims to determine the most accurate and practical method for anticipating difficult airways [3].

Preliminary evidence suggests that airway ultrasound may offer superior predictive value compared to traditional clinical parameters. For instance, ultrasound can accurately measure soft tissue thickness and identify anatomical variations associated with difficult laryngoscopy, which might not be evident through clinical examination alone. This capability is particularly beneficial in emergencies where patients may have anatomical challenges or conditions that complicate airway management [16].

Moreover, airway ultrasound can standardize the assessment process, reducing interobserver variability that often affects clinical examination. While clinical parameters rely heavily on the practitioner's experience and skill, ultrasound provides objective measurements that can be consistently reproduced. This standardization can lead to more reliable predictions and better preparation for managing difficult airways [11,17].

If airway ultrasound proves to be more reliable and accurate in predicting difficult laryngoscopy, it could significantly impact clinical practice in the ED. Emergency physicians could incorporate ultrasound into their routine airway assessment protocols, enhancing their ability to quickly identify patients at risk for difficult laryngoscopy. This early identification can lead to improved preparedness, including the use of advanced airway management techniques, alternative intubation strategies, and the involvement of more experienced personnel when necessary [18].

